### Randomization

2.6

Following the baseline study visit, all participants were randomly assigned to one of the two study groups using a 1:1 randomization method. The randomization process involved using a random number table method.

Here’s the specific randomization process:

#### Random number generation

2.6.1

A simple randomization method was used. The study designer generated a random number sequence using the RANDBETWEEN formula in Excel to create a sequence of numbers.

#### Sealed envelopes

2.6.2

The sequences of numbers were kept in identical outer, sealed, opaque, numbered envelopes.

#### Enrollment process

2.6.3

When each participant was enrolled, the researcher opened the envelopes sequentially according to a defined process.

#### Assignment

2.6.4

The participant was then assigned to the corresponding group based on the number in the opened envelope, and the researcher made a record of the assignment results.

### Interventions

2.7

The intervention content is grounded in mindfulness-based interventions (MBIs) and consists of six weekly themes designed to foster positive psychological states and healthy lifestyle routines among pregnant women. It integrates elements of the Individual and Family Self-Management Theory (IFSMT) and mobile-health strategies by leveraging the video-recording function of the WeChat app on smartphones: participants, accompanied by family members, record mindfulness videos on the assigned themes.

The multidisciplinary research team comprises one obstetrician, one obstetric nurse, and two research assistants. The obstetrician primarily handles maternal sudden illnesses and adverse reactions during pregnancy, while the obstetric nurse delivers positive thinking training tailored to specific intervention topics each week and addresses nursing and healthcare needs and precautions for pregnant women. The research assistants undertake various tasks, including registering study participant information, distributing and collecting questionnaires, disbursing subsidies. They also organize WeChat online video communications, downloading accompanying videos, and coordinating study follow-up visits.

The six-week Family Accompaniment Positive Thinking Intervention Program included six themes: 1) Understanding the Mindfulness-based Interventions Based on Family Accompaniment; 2) Speaking out about worries during pregnancy and childbirth; 3) How to better cope with adverse emotions during pregnancy and childbirth; 4) Familiarizing with the hospital’s maternity check-up process; 5) Each other in our eyes; and 6) Learning about maternal health. The specific intervention topics are detailed in **Table 1**.

**Table 1 T1:** Detailed Description of Intervention Themes.

Item	Theme	Explanation	Content of Implementation	Feedback
1	Understanding the Mindfulnes-based Interventions Based on Family Accompaniment.	Let pregnant women understand what mindfulness training is; The reason to do mindfulness training; What mindfulness training can achieve; Why family care is needed and what family care can do.	Obstetric nurses explain the current domestic and foreign intervention methods for maternal depression to pregnant women. The obstetrical nurses introduce the content of Mindfulness-Based Interventions theory and individual & family self-management theory. Encourage pregnant women and their caregivers.	Send videos about “The Understanding of Companion video sharing based on Family- Support.”
2	Expressing Worries During Pregnancy and Childbirth.	Grounded in personalized-care theory, the causes of depression differ for each pregnant woman. By collecting the worries voiced by pregnant women and their companions, we develop targeted intervention strategies or provide individualized counseling to alleviate these concerns.	Guided by a nurse, the pregnant woman and her companion each express their worries about pregnancy and childbirth—for example, unfamiliarity with hospital procedures, lack of prenatal and postpartum knowledge, concerns about physical recovery, or fears about not being able to care for the baby adequately alongside family members. After worries are gathered, any existing coping or problem-solving strategies are shared through recorded videos.	Send videos about “Worries &Strategies”
3	How to cope with perinatal bad moods.	It is quite common for negative emotions to occur during pregnancy and childbirth; therefore, it is crucial to help women during the perinatal period master effective coping strategies to maintain their emotional well-being.	(1) Promote physical and mental activities: Pregnant and postpartum women should participate in appropriate physical activities, such as yoga and walking. (2) Maintain good sleep and dietary habits: Sleep and diet are vital for emotional well-being. It is recommended that women during the perinatal period maintain a regular routine and keep a balanced and nutritious diet. (3) Build a social support system: Establish a social support network for women during the perinatal period that includes family, friends, and colleagues, as their support and understanding are particularly critical for emotional management. Additionally, these strategies can significantly improve emotional health during this critical time.	Send videos about “One day vlog during pregnancy (exercise video / diet sharing / family companionship).”
4	Familiarize Yourself with the Hospital’s Prenatal Examination Process	Enhance pregnant women’s trust in the hospital, help them become familiar with the routine prenatal examination procedures, and improve the compliance of both the pregnant women and their companions.	(1) A nurse explains the hospital’s routine prenatal examination items and procedures. (2) The pregnant woman and her companion record a video titled “Hospital Prenatal Visit Walk-through.”	Send videos about “Hospital Prenatal Visit Walk-through.”
5	“The mutual perception in our eyes”	Grounded in family-centered support, the relationship between the pregnant woman and her partner (especially her husband) is pivotal. This session aims to help both parties recognize each other’s contributions during pregnancy, identify shortcomings, and resolve conflicts, laying the groundwork for the partners’ understanding and active participation in the intervention.	(1) A nurse explains the physical and emotional changes pregnant women experience. (2) The nurse guides the caregiver on how to collaborate for a safe and joyful pregnancy, highlighting common pitfalls such as insufficient partner support, criticism, and excessive maternal caloric intake leading to macrosomia.	Send videos about “Changes and Feelings About Each Other.”
6	Understanding Delivery	Help pregnant women recognize the delivery process, alleviate anxiety, enhance confidence, improve self-care awareness, actively participate in delivery, ensure maternal and infant safety, and make informed decisions to smoothly welcome the infant.	(1) Detailed introduction to the three stages of labor: cervical dilation stage, fetal delivery stage, and placental delivery stage, as well as possible situations and pain experiences in each stage; (2) Educational courses and lectures: Organize or recommend pregnant and puerperal women to participate in educational courses and lectures about the delivery process; (3) Watch educational videos: Provide educational videos about the delivery process for pregnant and puerperal women.	Send videos about "Understanding Delivery."

The intervention program comprised six themes, and each theme lasted a week and delivered via WeChat. It involved teaching on specific themes and filming videos. At the beginning of each week, the obstetric nurse presented the week’s theme content to the pregnant woman and her companion. She also provided relevant introductory materials, such as texts and videos. Pregnant women and their companions were asked to record a companion video related to family support for each theme and send it to the research group’s WeChat. Research assistants managed the videos to ensure they met the study criteria, and they will provide feedback when necessary. At the end of each week, there was a WeChat online video exchange where pregnant women and companions could ask the research team about perinatal clinical and nursing problems encountered during the week, and the team responded individually. Additionally, pregnant women completed a questionnaire via WeChat at each follow-up site.

The inclusion criteria for companion videos required both the pregnant woman and caregiver to appear in the video. They needed to describe and record content based on the weekly theme. Additionally, at least three companion videos had to be completed during the six-week intervention period, with each video filmed at intervals of one week or more. Exclusion criteria for companion videos included: repeated sharing of the same video; presence or speech by only one person; and videos shorter than one minute.

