##### Adherence to companion video sharing

2.10.2.3

Adherence to the companion video sharing intervention will be assessed based on the frequency and consistency of video sharing by each pregnant woman.

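### The one-week spacing rule for companion videos does not fit one video per theme week and, read literally, understates adherence (minor)

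*Protocol article*

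**What the plan says.** All of the relevant text is in the protocol article.

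- **Section 2.7, schedule.** "The intervention program comprised six themes, and each theme lasted a week". Women and companions "were asked to record a companion video related to family support for each theme", which makes six videos over six weeks.
- **Section 2.7, criteria for videos.** "The inclusion criteria for companion videos required both the pregnant woman and caregiver to appear in the video". The same paragraph adds that "at least three companion videos had to be completed during the six-week intervention period", "with each video filmed at intervals of one week or more". It then lists grounds for rejection: "Exclusion criteria for companion videos included: repeated sharing of the same video; presence or speech by only one person; and videos shorter than one minute". Research assistants are to see that videos meet the study's criteria.
- **Section 2.10.2.3.** Adherence is a secondary outcome that "will be assessed based on the frequency and consistency of video sharing by each pregnant woman".
- **Section 2.1.** Acceptability and feasibility of video sharing are study aims.
- **Section 2.8.** Women are prompted by SMS and telephone in each intervention week to engage with that week's video content at times set in advance.

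**The concern.** A weekly theme and a seven-day minimum gap are different rules. The schedule lets a woman film on any day of each theme week. The spacing rule lets her film no earlier in a theme week than she did in the week before. If she films theme 1 on the last day of its week and theme 2 on the first day of the next, she has done what was asked, yet the two videos are one day apart and the second breaks the spacing condition.

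The adherence measure is at stake. One assessor counting themes covered and another applying the spacing literally could record different numbers for the same woman, and the literal count would be the lower one. The three-video minimum adds to the uncertainty: it is a count per woman placed among criteria for single videos, and the text does not say what it is for.

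**Working it through.** The document gives no figure for the video rule, so there is none to reproduce. The check asks how often on-schedule filming breaks the spacing rule.

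**Inputs from section 2.7:** six themes of 7 days each (42 days), one video per theme, minimum gap 7 days, minimum count 3.

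**Assumptions:** each of the 7 days of a theme week is equally likely, weeks are independent, and a video counts if filmed at least 7 days after the last counted one. Counting forward in this way retains as many videos as a seven-day gap allows, so it is the lenient version of a literal reading.

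**Step 1: can both rules be met?** Yes. Filming on days 1, 8, 15, 22, 29 and 36 gives six videos within 42 days, each exactly 7 days after the one before.

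**Step 2: when do they collide?** If the filming day within week k is d(k), from 1 to 7, the gap to the next video is 7 + d(k+1) − d(k). It is below 7 whenever d(k+1) < d(k). With uniform days this happens in 21 of 49 pairs, or 3/7 = 43%.

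**Step 3: how often do all six count?** The filming day must never move earlier in the week. The number of such patterns is C(12,6) = 924 out of 7^6 = 117,649, or 0.8%.

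**Step 4: full distribution for a woman who films all six themes** (exact enumeration):

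| Videos counted | Share of patterns |
|---|---|
| 3 | 7.9% |
| 4 | 62.6% |
| 5 | 28.7% |
| 6 | 0.8% |

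Mean = 3 × 0.0787 + 4 × 0.6264 + 5 × 0.2870 + 6 × 0.0079 = 4.22. As a check, exactly three count only if the second, fourth and sixth videos are each rejected, which has probability (3/7)^3 = 27/343 = 7.9%.

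**Step 5: sensitivity to the filming-day assumption.** If filming is confined to days 5–7 of each week, all six count in C(8,6)/3^6 = 28/729 = 3.8% of patterns and the mean is 4.48. If every video is filmed on the same weekday, all six count.

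**Step 6: effect on the three-video minimum.** Videos two theme weeks apart are at least 14 + 1 − 7 = 8 days apart.

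- Five or six theme videos: the first, third and fifth always satisfy the spacing, so at least three always count.
- Four theme videos: the probability that at least three count averages 0.93 over the possible sets of weeks. The lowest value is 0.82, for example weeks 1, 2, 4 and 5: 1 − (3/7)^2 = 40/49.
- Three theme videos: the average is 0.59. For three consecutive weeks it is C(9,3)/7^3 = 84/343 = 24.5%.

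**The case against.** The best defence is that the spacing qualifies only the minimum: at least three videos, spread out rather than filmed in one sitting. Insufficient spacing is not among the listed grounds for rejecting a video, and section 2.10.2.3 does not say that closely spaced videos are discarded. The defence also holds that asking for six and requiring three is a target and a minimum, and that prompts at set times (section 2.8), with a nurse's presentation at the start of the week and an online exchange at its end, make random filming days unrealistic.

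Much of this stands. Three against six is no contradiction, the two rules can be met together, and a regular weekly slot shrinks or removes the loss. The sentence can be read as the defence proposes, and then the count for a woman with five or six videos is not reduced. The text does not settle that reading, however, and the rule still misfires under it: a woman who films three consecutive themes on schedule satisfies it in only about a quarter of patterns. Section 2.8 sets times for engaging with the content; it does not say that filming is tied to one weekday.

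A reader might also infer that women with fewer than three videos are removed from the analysis, and, since only the intervention group films videos, that the comparison is biased in its favour. The document does not support this. The criteria are for videos, a shortfall below three is not a listed ground for exclusion, and neither the participant exclusion criteria (section 2.4.2) nor the statistical methods (section 2.12) contain an adherence condition. The analysis set may be defined in a statistical analysis plan that is not shown, so its absence here is no finding.

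**Conclusion.** The point holds in a narrow form and is minor. Read literally, the interval rule rejects some videos that follow the weekly schedule and so understates adherence. For a woman who completes every theme, about 4.2 of 6 videos count with uniformly random filming days, 4.5 if filming falls in the last three days of each week, and all 6 with a fixed weekday. These figures rest on the assumed filming days and on counting forward from the last accepted video; the document fixes neither. Under that counting, a woman with five or six theme videos is never placed below the three-video minimum, while a woman with three or four can be. The consequence is confined to the secondary adherence outcome and the feasibility aim. The primary comparison is not affected by anything that the document states.

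**What to change.** In section 2.7, replace the one-week interval condition with a rule that at most one valid video is counted per theme week. This still prevents several videos from one sitting being counted in the same week. In section 2.10.2.3, define adherence as the number of valid videos out of six, and label three or more as the minimum-adherence threshold, used descriptively. State there that the threshold does not decide who is analysed.

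The cost is two or three sentences and no new data: the shared videos are stored under section 2.13.2 and can be recounted. Section 2.15 requires protocol modifications to go to the Ethics Committee in writing before they are implemented. The change is best made before adherence is tabulated.

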### Adherence and monitoring

2.8

The study adopted a multi-pronged approach to improve compliance with the intervention protocol. First, a dedicated prenatal education program was established to provide participants with a comprehensive curriculum, ensuring they understood the objectives and procedures of the intervention. Second, participants in the intervention group were supported by a specialized research team; the project team regularly sent notifications and responded to questions from pregnant women. Third, participants were notified by SMS and telephone each intervention week to prompt them to engage with video intervention content on specified topics at predetermined times. Finally, we implemented six weeks of interventions on different topics based on common issues encountered during pregnancy and enhanced compliance by increasing the diversity of interventions and participants’ interest in participation.

### Control group

2.9

Pregnant women in the control group receive perinatal health care materials prepared by obstetricians and obstetric nurses. These materials, provided weekly as text messages, images, or both via WeChat, are sent during the first six weeks after enrolment. Additionally, the research assistant sends reminders via WeChat to prompt them to complete questionnaires at each follow-up time point.

### Outcomes evaluation

2.10

#### Primary outcome

2.10.1

The severity of maternal anxiety and depression is primarily assessed by the Edinburgh Postnatal Depression Scale (EPDS), the scale was developed by Cox et al. (53) in 1987 and introduced in 1998. The revised EPDS consists of 10 items, each divided into 4 levels: “Never,” “Occasionally,” “Often,” and “Always,” corresponding to scores of 0, 1, 2, and 3, respectively, with items 1, 2 and 4 being reverse scored. The total score ranges from 0 to 30. The Cronbach’s alpha coefficient of this scale is 0.87, indicating high validity and reliability (54). The Chinese EPDS-Dep-5 scale used in this study consists of items 1, 2, 8, 9, and 10 from the EPDS scale, and the cutoff score for the EPDS-Dep-5 scale is 4 points, meaning that when the total score of the assessment is ≥4 points, it indicates that the pregnant woman is at high risk for depression. Although the full version of the EPDS is more commonly used, this study chose the EPDS-Dep-5 mainly based on the following considerations: (1) This 5-item short version, which has been shown to be highly correlated with the full version (r≈0.90), does a good job of distinguishing depression in terms of sensitivity and specificity; (2) The sample size of this study is relatively small, and repeated assessments during the intervention process require a shorter version to reduce participant burden and reduce the chances of losing participants; (3) The short version can be completed in just 0.5–1 minute, making it better for new moms in the early days when they might not have much energy.

#### Secondary outcomes

2.10.2

##### Social support and psychological well-being

2.10.2.1

The Chinese Generalized Anxiety Disorder Scale (CGAD)will be used to measure the severity and functional impact of maternal anxiety in the last two weeks. The scale was developed by Spitzer et al (55). The scale consists of seven mood entries. Each entry is categorized into four levels: 0 means not at all, 1 means several days, 2 means more than a week, and 3 means almost every day. The scale has a total score of 21 points. Scores of 0–4 indicate no anxiety; 5–9 indicate mild anxiety; 10–14 indicate moderate anxiety; and scores above 15 indicate severe anxiety. The higher the score, the higher the score, the higher the degree of anxiety. Spitzer et al. (55) found that in a large sample survey, when using a score of 10 as the cut-off point, it had a sensitivity and specificity of 89 per cent and 82 per cent, respectively. The scale has a high Cronbach alpha coefficient of 0.92, indicating strong reliability and validity.

The Chinese Perceived Stress Scale (CPSS) will be used to assess the degree of perceived stress in mothers who perceive their lives as unpredictable, uncontrollable, or overloaded. The scale is divided into 4 entries, each of which is classified into 5 levels, ranging from 0 = “never” to 4 = “very often”. For scoring, a Likert 5-point scale is used, with 2 entries scored as forward scoring questions (1, 4) and 2 entries scored as reverse scoring questions (2, 3). Higher scores indicate higher perceived stress. The Cronbach’s alpha coefficient for this scale is 0.754 (56).

Maternal sleep quality will be assessed using the Chinese Pittsburgh Sleep Quality Index (CPSQI), the scale developed by Buysse et al. (57) in 1989 to assess the patient’s sleep over the past 1 month. The 19 individual entries yielded seven “component” scores, each of which was divided into four levels: sleep quality, time to sleep, sleep duration, sleep efficiency, sleep disorders, hypnotic medications, and daytime dysfunction (58). Entries 1 to 4 are subjective questions. Entries 5a to 5j, 7, and 8 are rated on a four-level scale: “none” scores 0, “<1 time/week” scores 1, “1–2 times/week” scores 2, and “≥3 times/week” scores 3. The response score for entry 6 is 0 points for “very good”, 1 point for “good”, 2 points for “poor”, and 3 points for “very poor”. The response score for entry 9 is 0 for “No”, 1 for “Occasionally”, 2 for “Sometimes”, and 3 for “Often”. The total score of the scale is the sum of the seven “component” scores, which range from 0 to 21, with a higher total score implying poorer sleep quality. A total score of more than 5 is considered to be sleep disturbance; a total score of more than 7 indicates poor sleep quality (59, 60).

Patients’ fatigue severity will be assessed using the Chinese Fatigue Severity Scale (CFSS), which has 9 entries. A Likert 7-point scale is used, with 1 indicating strong disagreement, and 7 indicating strong agreement. The average of the scores for the 9 questions is used for scoring. An average score of ≥4 indicates symptoms of fatigue. The higher the total score, the greater the degree of fatigue. The Cronbach’s alpha coefficient of the scale is 0.81 to 0.89, which has good reliability and validity (61).

The Chinese Family Health Scale Short-Form (CFHS-SF) is used to measure maternal family health functioning. The scale consists of 4 dimensions and 10 items. The 4 dimensions include: family/social/emotional health processes, family healthy lifestyle, family health resources, and external social support for the family. Each entry is scored on a 5-point scale ranging from “strongly disagree” to “strongly agree” (on a scale of 1 to 5), with questions 6, 9, and 10 being reverse scored. The higher the total score, the better the level of maternal family health. The Cronbach’s alpha coefficient for this scale is 0.846 (62, 63).

The level of social support will be assessed by the Chinese Perceived Social Support Scale (CPSSS). The scale consists of 3 dimensions and 12 items. The 3 dimensions include family support (items 3, 4, 8, and 11), friend support (items 6, 7, 9, and 12), and other support (items 1, 2, 5, and 10), and each item is rated on a 7-point scale (1 to 7). For positive scoring, each item is rated on a 7-point scale (1 = “not at all compatible”, 7 = “fully compatible”). The higher the total score, the higher the level of social support. Scores from 12 to 36 indicate low support, 37 to 60 indicate intermediate support, and 61 to 84 indicate high support (64).The Cronbach’s alpha coefficient for this scale is 0.925, which has high validity and reliability (65).

The Chinese Big Five Personality Inventory Brief Version (CBF-PI-B) will be used to evaluate the effect of maternal personality. This inventory consists of 5 dimensions and 40 personality items. These dimensions are neuroticism, extraversion, openness, agreeableness, and conscientiousness. Each item is scored on a 6-point scale: 1 = not at all, 2 = mostly not, 3 = somewhat not, 4 = somewhat, 5 = mostly, and 6 = fully. Each dimension is treated as a separate subscale and each subscale is scored separately. High and low score thresholds for each trait are as follows: neuroticism ≥ 25.9 (high), ≤ 8.5 (low); extraversion ≥ 28 (high), ≤ 17.3 (low); openness ≥ 31.3 (high), ≤ 21.3 (low); agreeableness ≥ 32 (high), ≤ 20 (low); conscientiousness ≥ 29.3 (high), < 24 (low) (66). The scales showed good internal consistency, with an average coefficient of 0.793. Test-retest reliability over 10 weeks averaged 0.742, indicating high reliability and validity (67).

